### Secondary outcomes measures

#### Motor learning

Motor learning in children will be assessed by means of the score obtained in the games. Individual scores in each of the six games from the second session (pre-test) will be summated as well as those from the six games of the last session (post-test) to obtain the general measurement of motor learning due to the treatment.

Individual scores in each game and for domain will also be counted (Manual Dexterity, Aiming and Catching, and Balance), before and after intervention. With the purpose of analyzing whether some activities are better learned in one type of intervention than in another. A specific form will be available for each therapist fills this information in each session.

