## Abstract

**Background:**

Despite the benefits highlighted by motor interventions based on virtual reality for children with Developmental Coordination Disorder (DCD), there are still doubts as to whether these are greater than those obtained with conventional interventions due to the absence of systematized protocols, and lack of evidence. Here, we present a protocol to systematically compare the effects of two motor-training programs (one Nintendo® Wii-based and the other no-Wii motor activities) on the motor learning in children with DCD.

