More specifically, the use of the Nintendo® Wii in the rehabilitation of children with motor alterations has been promoted for ease of measuring the force applied and capturing pressure change available in the Wii Balance Board (WBB), besides the fact that the Wii motion control allows great stimulation of the hand-dexterity motor component [15, 16]. Balance, Aiming and Catching are the domains of the Movement Assessment Battery for Children (MABC), that are regarded as the gold standard for the identification of DCD in children [17]. These aspects make the Nintendo® Wii very useful as a VR resource for motor interventions in children with DCD.

At present, however, little evidence exists in the literature on comparisons between the benefits of VR training, such as Nintendo® Wii, and conventional interventions such as without Wii [18–20].

The handful of existing studies that compare interventions with and without VR for children with DCD still show limitations about evidence created by the VR intervention [19, 21–24]. Moreover, it is not clear whether one type of intervention offers greater gains than the other due to the shortcomings from the scarce previous studies already published. Based on a recent systematic review by Hickman et al. [25] evidence for advantages gained by a VR intervention for children with DCD are not consistent in relation to conventional therapy. The authors argued that due the heterogeneity of assessment tools and outcomes fair comparisons were not possible. So, we believe that in this study we might see fair comparisons because the tasks will be closely matched by motor domain target into the training protocol.

These limitations of present approaches hinder a well-informed conclusion as to whether training with VR is more effective than conventional training in children with DCD. In this paper we present a protocol for a randomized clinical trial to systematically compare two motor-training programs (with and without Nintendo® Wii) on motor learning in children with DCD.

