### Frisbee

This activity will be performed with the children holding the Wiimote control in the fist, in a space of 1.10 m^2^, at a 2-m distance from the television screen to which the Nintendo® Wii will be connected, performing throws of the virtual Frisbee, aiming to hit the target in the scoring area projected.

Children will be encouraged to perform the highest number possible of throws in the period of 7 min, trying to hit the scoring areas worth 10, 50, and 100 points. Every time the Frisbee hits these spaces, it will count as a hit and as a mistake each time it hits outside them. The sum of all attempts hitting any scoring area during 7 min in each session will be the basis of the score.

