### Marble balance

This activity will be performed with the WBB equipment fixed to the ground, similar to what described for the tightrope walk. Children will move their trunk to different positions while trying to throw the ball in the holes of the virtual platform, which will be turning all the time, provoking greater unbalance and difficulty in the game. Every ball falling out of the virtual platform will count as an error, and each one in the respective hole will be worth a point. As the balls disappear, the children will move to a new platform, with more balls to be thrown into the holes. Scores will be calculated by the Nintendo® Wii equipment itself with basis on the performance of the avatar commanded by the children.

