### Balance disk

This activity will be performed with a vinyl balance disk measuring 40 cm in circumference (Fig. 6) placed on the ground; the children will perform 14 different static balance postures on top of it (Table 4). The postures were based on, and adapted from, the Berg Balance Scale [28]. Children aged 7 and 8 years must maintain the postures for 15 s, while 9- and 10-year-old children must keep them for 30 s. Each posture performed correctly and for the time due will count as a hit, while unbalances, falls, stepping on feet or putting hands on the ground will be regarded as mistakes. In the second case, children must go to the following posture. Each hit will be worth 10 points, and at the end of the 14 postures, they will repeat the same sequence until the time is over.

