## Discussion

This study protocol is the first to directly compare the efficacy of two motor-training protocols in children with DCD. The protocol is based on the domains of the MABC-2 domains. Various studies have already demonstrated the efficacy of intervention programs based on VR for these children [19–24, 31–36], but the absence of further protocol systematization has been an important hindrance for professionals and researchers in this field to clearly understand the impact of such interventions on children’s activity performance.

Studies comparing interventions based on VR and conventional interventions [19, 22–24] are scarce, and their results tend to demonstrate that despite the benefits of VR, conventional interventions seem to be more effective in the improvement of motor performance of children with DCD [19, 22–24]. Due to limitations and differences between the protocols adopted, though, these results must be interpreted carefully. Hence, when testing the efficacy of these two type of intervention programs, planned in similar manner, with similar scoring systems and activities, it will be possible to enhance evidence about the benefits in motor performance and learning of one program over the other.

One documented advantage of VR training, such as the Wii intervention, is the motivating aspects because the projected architecture on the environment of VR is capable of hold the children’s attention, being an important aspect for rehabilitation of children with DCD [20].

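### Motor learning is a raw sum of six game scores on point scales differing up to 100-fold, and three of the six game pairs have no common unit for the planned comparison between arms

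*Protocol article*

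**What the plan says.** The Abstract presents a protocol "to systematically compare the effects of two motor-training programs (one Nintendo® Wii-based and the other no-Wii motor activities) on the motor learning", and the Background ends by saying that the trial will "systematically compare two motor-training programs (with and without Nintendo® Wii) on motor learning in children with DCD". The outcome sections nevertheless make the MABC-2 total standard score primary and list motor learning as secondary.

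The Motor learning section defines the outcome: game scores from the second session are added over the six games, and they "will be summated as well as those from the six games of the last session (post-test) to obtain the general measurement of motor learning". The Interventions section defines a session's score as points added over all attempts. Neither section mentions weighting or standardisation.

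Scores per game and per domain are also kept, "With the purpose of analyzing whether some activities are better learned in one type of intervention than in another". Statistical methods includes motor learning in the comparisons between groups, by ANOVA and ANCOVA or by the Mann-Whitney test. The Discussion describes the two programmes as "planned in similar manner, with similar scoring systems and activities" and expects evidence on performance and learning of one over the other.

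**The concern.** A raw sum gives most weight to the component with the largest points and spread. Here the weights come from the scoring rules of the games, not from any judgement about which skills matter. A change in the total may then say little about balance or table tennis.

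A comparison of arms adds a second difficulty. A common ANCOVA slope, or ranks pooled over both arms, presupposes that a point means the same thing in each arm. Where paired games pay different amounts for a success, or count different events, equal learning can produce unequal scores. The question named as the trial's aim would then be answered on an outcome poorly suited to it.

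**Working it through.** **Plan's own figure.** The article gives no expected score, standard deviation or number of throws for motor learning. Its one computed figure, 15 per group, reproduces for a two-sided paired t-test with effect size 0.80 (power 0.821). It rests on the MABC total and does not bear on this point.

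**Step 1: points per scoring event** (activity descriptions, Wii and no-Wii).

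| Pair | Wii | No-Wii |
|---|---|---|
| Frisbee | 10, 50 or 100 | 10, 50 or 100 |
| Table tennis | one hit per point won against the machine | one hit per solo rebound off the raised half |
| Bowling | pins, with strike and semi-strike bonus | 1 per bottle, same bonus |
| Archery / bow and arrow | 1 to 10 | 1 to 10 |
| Tightrope / beams | 15, 20, 10 | 10, 15, 20 |
| Marble balance / disk | 1 per ball | 10 per posture |

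For Wii Frisbee the child throws, "trying to hit the scoring areas worth 10, 50, and 100 points". For marbles, "each one in the respective hole will be worth a point". The largest ratio is 100/1 = 100, and even the lowest Frisbee hit is worth 10/1 = 10 marbles.

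**Step 2: Frisbee's share of the total.** With h hits at a mean of m points, and R points from the other five games, share = hm/(hm + R). All values of h, m and R are assumptions.

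- Middle case, h = 20 and m = 30, so hm = 600.
  - Wii: R = 20 (table tennis) + 80 (bowling) + 100 (archery) + 25 (marbles) + 60 (tightrope) = 285. Share = 600/885 = 68%.
  - No-Wii: R = 50 + 80 + 100 + 120 (disk) + 90 (beams) = 440. Share = 600/1040 = 58%.
- Lowest case, h = 5 and m = 10, with high scores elsewhere. Wii: 50/(50 + 555) = 8%. No-Wii: 50/(50 + 880) = 5%.
- Highest case, h = 40 and m = 53.3, with low scores elsewhere. Wii: 2133/(2133 + 113) = 95%. No-Wii: 2133/(2133 + 205) = 91%.
- Hits needed to pass half of the total at m = 30: R/30, about 10 (Wii) and 15 (no-Wii) in the middle case.

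A simulation with 15 to 45 throws, and assumed spreads for the other games, put Frisbee at 28% to 88% of the mean total and 72% to 99% of the between-child variance.

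In the middle case, a 20% improvement in every game raises the total by 20%. Frisbee supplies 0.2 × 600/885 = 13.6 of those percentage points in the Wii arm and 0.2 × 600/1040 = 11.5 in the no-Wii arm. Table tennis supplies 0.5 and 1.0.

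**Step 3: the domain score.** Manual Dexterity is Frisbee plus table tennis. In the middle case Frisbee is 600/620 = 97% of it (Wii) and 600/650 = 92% (no-Wii). With 5 ten-point hits and high table-tennis scores it is 50/90 = 56% and 50/150 = 33%.

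**Step 4: units across arms.**

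- Five more successes in the second balance game add 5 × 1 = 5 points with Wii and 5 × 10 = 50 without.
- Tightrope and beams both pay 45 for all three parts. One part completed pays 15 against 10, and two parts pay 35 against 25.
- Only the no-Wii descriptions vary with age: bowling distance (4.83 or 6.03 m), arrow distance (2.30 or 2.97 m) and the disk, where "Children aged 7 and 8 years must maintain the postures for 15 s, while 9- and 10-year-old children must keep them for 30 s". In 420 s, ignoring transitions, the disk ceiling is 420/15 × 10 = 280 points for younger children and 420/30 × 10 = 140 for older ones.

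**The case against.** A reader might infer that the total is mostly Frisbee. The article does not support that as a fact. With few hits, or mostly ten-point hits, Frisbee is a minor part, and the high variance shares also rest on assumed play. The Wii Frisbee description adds doubt: it bases the score on the throws that land in a scoring area, which can be read as counting hits. The sum of points in the Interventions section points the other way. If hits were counted in the Wii arm only, Frisbee too would lose its common scale.

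A reader might also infer that every game is scored differently by arm. Frisbee, bowling and archery share a nominal scale, so a Frisbee-dominated total would be dominated by a game with the same points in both arms. That is fair, but such a total would no longer measure learning over six games, and virtual and real throws need not allow the same number of attempts in 7 min.

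The scores per game and per domain mean that changes in balance would not be lost. This stands, with two limits: the Manual Dexterity domain repeats the Frisbee problem, and the per-game comparison of marbles with disk still sets 1 point against 10. Cohen's d is free of units within an arm, but a between-arm d on raw points is not.

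The disk ceiling overstates the effect of age. It assumes that every posture is held, and before and after scores come from the same child, normally under one hold time, so much of it cancels in relative change.

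Finally, motor learning is secondary. It would go too far to say that the trial's main result is compromised.

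**Conclusion.** The concern holds in limited form. It rests on the article's own definitions: an unweighted sum, a spread of up to 100-fold in points per event, and planned comparisons of these scores between arms. For three of six pairs the raw points have no common unit, so the Discussion's claim about scoring is only partly true. Followed as written, the plan could show an arm difference in motor learning that comes from scoring units.

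The size of Frisbee's influence is not established. It can dominate the total and the Manual Dexterity score, at 58% to 68% of the total under the middle assumptions and 5% to 95% over the full assumed range. The sum and the comparison are stated in the article, so this is not a matter of detail left to an analysis plan. The primary analysis on the MABC-2, which both arms take in the same form, is unaffected.

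**What to change.** 1. In Motor learning, replace the raw sum. Divide each game's score, at both sessions, by that game's session-2 standard deviation within the arm. Average the two games in each domain, then the three domains.
2. Report motor learning mainly as within-arm change per game, per domain and in total.
3. In Motor learning and Statistical methods, drop tests of raw game points between arms. Label any comparison of standardised gains as exploratory, since these still depend on each arm's own baseline spread.
4. Base the conclusion on Wii against no-Wii on the MABC-2.
5. In the Discussion, qualify the statement on scoring by naming the pairs that differ.
6. Reconcile the Wii Frisbee scoring sentence with the sum of points in Interventions.

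The scores needed are already recorded, so the cost is wording and analysis code. A firm between-arm claim on a secondary outcome is given up. Standard deviations from about 16 children per arm are imprecise: under normality the relative standard error is about 1/√(2 × 15) = 18%. Splitting by age band, at about 8 children each, would raise it to 1/√(2 × 7) = 27%, so they should not be split further. Whether to reword the trial's aim is a separate matter.

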**Methods/design:**

Two intervention protocols (one based on Nintendo® Wii and the other no-Wii motor activities) will be carried out, with interventions occurring twice a week in 60-min sessions, with a minimum of 12 and a maximum of 16 sessions per child.

The protocols were developed based on the domains of the Movement Assessment Battery for Children – Second Edition (MABC-2) (Manual Dexterity, Aiming and Catching, Balance), with two activities for each of the MABC − two domains. The study will include children aged 7 to 10 years with a total MABC-2 score ≤ 16, and a Developmental Coordination Disorder Questionnaire (DCDQ) score < 46 (age of 7 years), score < 55 (age group of 8 to 9 years and 11 months), or score < 57 (age of 10 years) as scored by the parents. Children will be randomly allocated by draw in one of the two intervention protocols. MABC-2 and DCDQ will be applied before and after intervention to evaluate the effects of the interventions on motor performance and parents’ perception, respectively. Motor learning will be assessed by means of the scores obtained in the games. Evaluators and therapists will be trained and evaluators will be blind regarding the data of the children in the study.

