### Outcomes measures

All tests will be applied by trained evaluators, blind regarding the allocation of the children in the intervention groups. Evaluators will be professionals in the areas of physiotherapy, physical education, and occupational therapy. Each child will be assessed by the same person before and after treatment.

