### Primary outcome measure

#### The primary outcomes of this study is the motor performance

##### Motor performance – MABC-2

The motor performance of the children will be assessed through the MABC-2 total standard score (TSS). As mentioned before, MABC-2 is considered a gold standard tool to identify motor performance problems in children from 3 years old. MABC-2 is divided in three different age bands: the band 1 for children aged from 3 to 6 years old; band 2 for children aged from 7 to 10 years old; and band 3 for children aged from 11 to 16 years old. There are eight tasks in total, three for the Manual Dexterity domain, two for the Aiming and Catching domain; and three for the Balance domain. Children received a specific score in each domain and their motor performance classification is based on total score and percentiles values. Children < 5° percentile present motor difficult; children < 16° percentile are at risk for motor difficult and children > 16° percentile have no motor difficult detected. According to the MABC-2 tester manual, each child spends about 30–40 min completing all tasks.

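### Game points from different tasks cannot show in which programme a domain's activities are better learned; the blinded MABC-2 domain scores should carry any domain-level comparison between arms

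*Protocol article*

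**What the plan says.** The primary outcome is motor performance, measured by the MABC-2 total standard score. On the parts of that test, the same section says: "Children received a specific score in each domain and their motor performance classification is based on total score and percentiles values". The abstract fixes the timing: "MABC-2 and DCDQ will be applied before and after intervention to evaluate the effects of the interventions on motor performance and parents’ perception". Under Outcomes measures the article adds: "All tests will be applied by trained evaluators, blind regarding the allocation of the children in the intervention groups".

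Motor learning is a secondary outcome, measured by game points at the second and last sessions. Besides the overall sum, the article plans scores at a finer level: "Individual scores in each game and for domain will also be counted (Manual Dexterity, Aiming and Catching, and Balance), before and after intervention". The reason follows: "With the purpose of analyzing whether some activities are better learned in one type of intervention than in another". On who records the points: "A specific form will be available for each therapist fills this information in each session". Design and general characteristics says that each programme has its own therapists.

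The Background rests its claim of a fair comparison on the design of the tasks, "because the tasks will be closely matched by motor domain target into the training protocol". Statistical methods refers to motor performance and learning in general terms and names no MABC-2 domain score.

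**The concern.** The article sets a between-programme question, by game and by domain, and assigns it to points that are earned on different tasks in the two arms. No child is scored on the other arm's tasks, so the programme and the measuring instrument cannot be separated. A larger gain in Balance points in one arm could reflect better learning, an easier game, more points per success, a lower ceiling or more generous recording.

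What is at stake is the domain-level secondary result. Both programmes are built on the three MABC-2 domains, so readers will look for a domain-level answer, and the only one the article names has no common scale. A measure with a common scale is already in hand, since every child receives MABC-2 domain scores.

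**Working it through.** **The plan's own figure.** Sample size asks for 15 per group from a within-group comparison with effect size 0.80, 80% power and 5% alpha. A two-sided paired t-test (noncentral t) with an effect of 0.80 gives n = 15, power 82.1%. The figure reproduces. It does not bear on this point except to fix the trial's size, read here as 16 per arm after the dropout allowance.

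**Game points side by side** (from the task descriptions; 7 minutes each)

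| Domain | Wii | No-Wii |
|---|---|---|
| Balance | Marble balance: 1 point per ball | Balance disk: 10 points per posture |
| Balance | Tightrope thirds: 15, 20, 10 | Beams: 10, 15, 20 |
| Manual Dexterity | Table tennis: points won against a machine | Table tennis: valid returns off a raised half-table, no opponent |
| Manual Dexterity | Frisbee: 10, 50, 100 | Frisbee: 10, 50, 100 |
| Aiming and Catching | Archery: 1 to 10 | Bow and arrow: 1 to 10 |
| Aiming and Catching | Bowling: pins with strike bonus | Bowling: bottles with strike bonus |

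- Balance disk ceiling, ignoring transitions: 7 min = 420 s. At ages 7–8, 420/15 = 28 postures, 28 × 10 = 280 points. At ages 9–10, 420/30 = 14 postures, 14 × 10 = 140 points. The scale halves with age inside one arm, and the Wii counterpart uses another unit altogether.
- Tightrope and beams: one full pass is worth 15 + 20 + 10 = 45 and 10 + 15 + 20 = 45. The totals agree, but the steps are weighted differently and the tasks are not the same.
- In the last three rows the point rules are alike, but the tasks are virtual in one arm and physical in the other. Archery, for instance, is shot at virtual distances of 10, 25 and 35 m against a real 2.30 or 2.97 m.

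**MABC-2 domain scores on the same criteria.** There is one instrument for both arms, with one age band covering 7 to 10 years. It is applied before and after by evaluators blind to allocation.

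**What 16 per arm can show** (two-sample t, two-sided, noncentral t)

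- Standardised difference detectable with 80% power: 1.02 at alpha 0.05 and 1.20 at alpha 0.05/3. Normal approximation as a check at 0.05: (1.96 + 0.84) × √(2/16) = 0.99.
- Power at an assumed difference of 0.8: 59% at 0.05 and 41% at 0.05/3.
- Power at an assumed difference of 0.5: 28% at 0.05 and 15% at 0.05/3. Baseline adjustment with an assumed pre-post correlation of 0.7 raises the effective difference to 0.5/√(1 − 0.49) = 0.70, with power of about 48% and 31%.

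**Illustration of what a total can mask** (weights assumed). Suppose Wii is better by 0.5 SD on Balance, worse by 0.5 SD on Aiming and Catching, and equal on Manual Dexterity. Equal domain weights give (0.5 − 0.5 + 0)/3 = 0. Weights by the number of tasks per domain (3, 2, 3) give (3 × 0.5 − 2 × 0.5 + 0)/8 = 0.06.

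**The case against.** The strongest reply is that the stated purpose concerns learning of the trained activities, which the article keeps apart from motor performance. MABC-2 domain scores do not measure that and cannot stand in for it. This is right, and it limits the fix: the game points stay as the learning outcome, read within each arm. It does not rescue the between-arm contrast. Dividing each arm's change by its own standard deviation would remove the units, but the result would still describe different tasks.

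A second reply is that the Discussion presents the two scoring systems as similar. For frisbee, archery and bowling the point rules are. They are not for table tennis or either balance task, so two of the three domain sums are affected by the rules as well as by the tasks. The statement that evaluators are blind might also be taken to cover the game points, but those are entered by the therapists delivering the session.

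Third, subscale analyses often sit in an analysis plan, and none is shown here. A reader might infer that the MABC-2 domain scores will never be compared between arms. The documents support only that this article names no such comparison. The point still stands, because the article itself gives the domain-level comparison to the game points.

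Finally, a reader might infer that the total score is the wrong primary outcome because domain effects could cancel. The documents do not support that. The Background cites features of the Wii that favour balance and hand dexterity and predicts no domain in which it does worse. The cancellation above is an assumed scenario, and any composite can mask opposing parts. Three corrected tests at this size would also usually miss differences of 0.5 SD.

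**Conclusion.** The concern holds for the secondary outcome. Comparing game and game-domain points between arms, as Motor learning proposes, confounds the programme with the task, partly with the scoring rule, and with unblinded recording by arm-specific therapists. No such contrast can be read as better learning in one programme. The bias cannot be given a size, because the points share no unit; the scoring table and the 280-point and 140-point ceilings show the mismatch.

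The MABC-2 domain scores are the better basis for a domain-level comparison, with two limits. They measure domain performance, not learning of the trained activities. At 16 per arm they give supportive estimates only, with 80% power reached at a difference of about 1.0 SD, or 1.2 SD at alpha 0.05/3. These figures assume a two-sample t-test with no gain from baseline adjustment; adjustment would help by an amount that depends on a correlation the article does not give.

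**What to change.** - In Motor learning, restrict the game and game-domain scores to describing change within each arm, and drop the aim of comparing them between programmes.
- Name the three MABC-2 domain scores as the secondary outcome for the domain-level comparison. For each, estimate Wii minus no-Wii at post-test, adjusted for that score's own baseline, with a 95% confidence interval and a correction over the three (Holm, for example).
- State that these estimates are supportive, that power is low at 16 per arm, and that they concern domain performance and do not replace the task-learning outcome.
- Leave the total score as the primary outcome.

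The cost is a change of wording and three more models on data already collected, with no new test or visit. If an existing analysis plan already contains these models, only the Motor learning text needs to change.
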